## **GLOSSARY OF ABBREVIATIONS**

|              |                                                              |
|--------------|--------------------------------------------------------------|
| BASEC | Business Administration System for Ethical Committees |
| CRF   | Case report form                                      |
| FOPH  | Federal Office of Public Health                       |
| HRA   | Human Research Act                                    |
| HRO   | Ordinance on Human                                    |

## 1 BACKGROUND AND PROJECT RATIONALE

The world is currently facing a pandemic caused by a highly pathogenic coronavirus, SARS-CoV-2, that induces a disease called COVID-19. Originally, it started from the city of Wuhan in China, but meanwhile, the virus has rapidly spread around the world, infecting more than 4 million people and causing more than 300'000 deaths so far.

Little is known about the neurotropism of SARS-CoV-2. Several other coronaviruses in mouse models and patients however have the potential to cause severe encephalitis. There are reports of anosmia in a considerable number of patients suffering from COVID-19. This might also suggest CNS involvement. Further, the profound respiratory depression in critically ill patients might be related to central respiratory dysfunction, with an underlying affection of the brainstem. A detailed neurological workup of the severely ill patients with CSF analysis and MRI imaging has not been published so far, but reports from centers in northern Italy suggest that neurological symptoms in COVID-19 patients are more frequent than previously assumed. Very recently, a case of acute hemorrhagic encephalitis in a COVID-19 affected individual was reported in the journal *Radiology*. Microglia — the only brain-resident immune cells — play an essential role in antiviral defense of the brain. These cells are resident macrophages of the brain parenchyma. They express relevant endosomal and cytosolic pathogen pattern recognition receptors for detecting viral molecules and are capable of efficiently sensing viral pathogens *in vitro*. Reactive microgliosis, defined as an increase in microglial numbers and a change from ramified to amoeboid morphology, is observed in both patients and mice with viral encephalitis. Whether microglial reactivity is an appropriate response to viral invasion, or contributes negatively to disease, continues to provoke debates. One additional COVID-19 entry receptor, CD147 (basigin, BSG), is expressed mostly on endothelial cells, astrocytes, and to a lower level on microglia in the brain, whereas ACE2 has generally low expression levels (<https://www.brainrnaseq.org/>). Interestingly, CD147 is upregulated under certain pathological conditions such as stroke, leading to blood brain barrier disruption and leukocyte infiltration, and its inhibition led to better outcomes in a mouse model of ischemic brain damage. Peripheral immune responses such as cytokine storm or other yet to be determined factors might therefore equally lead to upregulation of this entry receptor and facilitate viral spread into the CNS. To investigate the tumor microenvironment in glioblastoma, a malignant brain tumor, we recently established a microglia-focused, brain-specific 50+ marker CODEX panel. Using this panel, we were able to quantify the brain microenvironment composition and -reaction to specific therapeutic conditions in unprecedented depth. We will repurpose this panel to assess the neuroinflammatory microenvironment in specific brain regions of deceased COVID-19 patients, and provide an integrative view on yet unknown factors that facilitate neurotropism by taking into consideration clinical, neuroimaging, high-throughput cerebrospinal and plasma targeted proteomics.

## 2 PROJECT OBJECTIVES AND DESIGN

### 2.1 Hypothesis and primary objective

We hypothesize that the microglia reaction or direct neurotropic effects of CNS COVID-19 might play a pivotal role in pathogenesis and deleterious brain stem dysfunction in critically ill patients.

The peripheral (cerebrospinal fluid and peripheral blood) cytokine response to SARS-CoV-2 might be critical for CNS affection and consecutive blood brain barrier disruption leading to brain-inherent neuroinflammatory reactions.

## 2.2 Primary and secondary endpoints

- Evaluation of neurological/mental state and specific scores
- Systematic CNS MRI imaging to document specific changes due to COVID-19 infection
- Plasma and CSF cytokine targeted proteomics analysis
- Peripheral blood leukocyte CyTOF analysis
- CODEX (high dimensional microscopy) analysis and viral load/in situ distribution analysis of defined regions on brain autopsy specimens

Primary endpoints of this project are the multidimensional integration of the analysis from the procedures described above and assessment of the correlation between the gained clinical data (MRI, mental/neurological state), the body fluid proteomic and mass-cytometric analysis (CSF and Plasma proteomics, peripheral blood mass cytometry) and the CODEX analysis of defined brain regions on autopsy specimens. This will enable us to identify biomarkers that potentially predict CNS involvement of COVID-19 disease and tailor respective treatments.

## 2.3 Project design

The project flowchart is depicted below. Patients with confirmed COVID-19 disease specifically hospitalized for this disease as well as out-patients will be included. After patient informed consent, we will perform a detailed clinical-neurological assessment followed by blood and lumbar puncture, and MRI analysis. In case of disease-related death (assuming a case fatality rate on the ICU of 50%), an autopsy by the institute of pathology will be performed, encompassing high dimensional analysis of the organs under investigation.

[figure not shown]

**CSF and plasma cytokine proteomics and correlate to mental/neurological state.** CSF will be acquired by lumbar puncture and sent for routine analysis including CSF chemistry, cytology and microbiology. Targeted CSF proteomics using OLINK Proximity Extension Assay (PEA) technology (<https://www.olink.com/products/immune-response-panel/>), to assess a potential

CNS-contribution of the disease will be performed. A similar biomarker approach will be applied for plasma samples from the same time-point as the lumbar puncture. Already established CyTOF technology will be used to gain insight into the peripheral blood immune composition in both patient cohorts (CyTOF panel listed in table 3). Presence of viral RNA will be tested by our in-house qPCR in both plasma and CSF. We will include COVID-19 negative CSF and plasma samples from healthy reference patients into this analysis.

### **CyTOF (mass cytometry analysis) of peripheral blood leukocytes**

Already established CyTOF technology will be used to gain insight into the peripheral blood immune composition in both patient cohorts. Presence of viral RNA will be tested by our in-house qPCR in both plasma and CSF. We will include COVID-19 negative CSF and plasma samples from healthy reference patients into this analysis.

### **Systematic CNS MRI imaging to document early/manifest encephalitic changes in COVID-19 patients.**

Both patient populations will undergo 3 Tesla magnetic resonance imaging (MRI) in collaboration with our colleagues from neuroradiology (responsible: [name]). MRI sequences will include 3D T1 +/- gadolinium, FLAIR, diffusion, SWI and T2 weighted sequences to document potential early signs of encephalopathy, and will be correlated to CSF, plasma and clinical findings. Appropriate precautions will be taken to ensure the safety in the MRI scanner of patients with respiratory, neurological, or other types of dysfunction, and all necessary anti-infectious precautions will be observed before, during, and after the scanning of patients with known COVID infection.

### **High dimensional, microglia-centric CODEX fluorescent microscopy of defined brain regions on autopsy specimens from medulla oblongata, cortex, cerebellum, and olfactory bulb.**

We recently implemented a brain-specific CODEX panel for the assessment of the immune microenvironment, with inclusion of a wide array of myeloid/microglia markers, T-cell markers, and a few neuronal markers. All the antibodies have been validated and tested in formalin-fixed tissues of different zones of glioblastoma tumors including invading tumor periphery. The panel will be modified to include the viral entry receptors, CD147, ACE2 and TMPRSS2. Presence of SARS-CoV-2 virus particles will be assessed by qPCR, and MIBI technology will be used to visualize tropism of virus to specific cellular brain compartments. The downstream processing pipeline (segmentation, clean-up gating, clustering, neighborhood analysis, visualization and high-performance computing) have been established at our institution in the last year in the framework of a project funded by The Brain Tumour Charity, UK (grant number GN-000562).

Microglia reaction patterns, orchestrated with other CNS immune cells and in interaction with neuronal and glial counterparts, might play a crucial role in determining the severity of COVID-19, ultimately leading to central respiratory failure. We will be able to assess a multitude of phenotypic characteristics of the tissue reaction and neuronal/glial/immune cell crosstalk at once. Moreover, by having access to a wealth of clinical data including MRI images and CSF proteomics, we expect to find indicators/biomarkers for a worse clinical course resulting from microglial or other CNS-immune cell-mediated overactivity and/or neuronal death, which could be counteracted with CNS-specific treatments in the future.

## **3 PROJECT POPULATION AND STUDY PROCEDURES**

### **3.1 Project population, inclusion and exclusion criteria**

We will *prospectively* include 20 non-critically ill COVID-19 patients from the inpatient ward or from the ambulatory test centre, and 20 critically ill COVID-19 patients needing mechanical ventilation at the ICU. Neurological assessment will be performed by a board-certified neurologist using NIHSS (National Institute of Health Stroke Scale) scoring and other standard neurological tests. Neurological symptoms will be carefully documented. Assuming a case fatality rate of 50% in the critically ill group, we anticipate to include 10 patients for *post mortem* analysis of brain regions, some of which might be neurologically affected.

The following inclusion criteria are going to be applied: COVID-19 positive tested.

The following exclusion criteria are going to be applied: COVID-19 negative tested, patients under 18 years old, pregnant women.

A pregnancy test is performed and documented for women of childbearing age

Concerning the out-patients they will only be included if they have the option to come to the hospital by car, bike or if they live close enough to walk. In case public transport is their only option they can not be included.

To avoid conflicts and to identify parallel participation of individual USB patients in several studies, the DKF (Departement Klinische Forschung) has created a web application.

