## **6.2 Risk-Benefit Assessment**

Risks of the procedures in this project:

- MRI: allergic reaction to contrast agents
- Lumbar puncture: Infection, post-lumbar puncture headache
- Blood withdraw: Infection.

Each of the mentioned risks takes place in less than 1%. To reduce the risk of infection the procedures of lumbar puncture and blood withdraw are kept under sterile conditions (disinfection, sterile gloves, protective masks etc.). During MRI procedure the participant is observed by specialized employees.

Results of the project could benefit future patients infected with SARS-CoV-2. We could better understand the mechanisms that take place during infection with SARS-CoV-2, identify predictive markers for severe course and building on these findings new treatment approaches could be generated.

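### Sections 2.3 and 3.1 disagree on which inpatients qualify, so a patient admitted for another brain disease with an incidental positive test can enter the neurologically affected group

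*Protocol*

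**What the plan says.** Protocol section 2.3 describes the population as follows: "Patients with confirmed COVID-19 disease specifically hospitalized for this disease as well as out-patients will be included". For inpatients, the reason for admission is part of the definition.

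Protocol section 3.1 is the list that recruiters apply. Its single inclusion criterion is "The following inclusion criteria are going to be applied: COVID-19 positive tested", and its exclusions are "COVID-19 negative tested, patients under 18 years old, pregnant women". For out-patients it adds a travel restriction: "In case public transport is their only option they can not be included". The cohorts are to "include 20 non-critically ill COVID-19 patients from the inpatient ward or from the ambulatory test centre, and 20 critically ill COVID-19 patients needing mechanical ventilation". Reason for admission does not appear, and neither does previous or concurrent neurological disease. Section 3.2 (recruitment and consent) does not restore the condition.

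Section 4.1 has neuroradiologists report encephalitic changes that may be related to COVID-19. It then singles out, as the most important comparison, neurologically affected against unaffected patients with respect to CNS involvement. The CSF and plasma reference samples in section 2.3 come from healthy, COVID-negative people.

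**The concern.** Two sections of one protocol give different answers for the same inpatient. Someone brought to the ward or the ICU with, say, a stroke, a seizure or a head injury, and found positive on testing, fails 2.3 and passes 3.1. Sites usually screen against the criteria list, so 3.1 is likely to prevail.

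This matters because the study asks what COVID-19 does to the CNS. A patient with another brain disease has a neurological deficit for that reason and would tend to be classed as affected. The proportion classed as affected then rises for a cause other than COVID-19. The marker contrast between affected and unaffected patients also becomes a mixture. It may be diluted, or it may pick up markers of the other disease. Healthy reference samples cannot separate the two causes, because no comparison group has CNS disease without COVID-19.

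**Working it through.** **The plan's own figures.** Section 3.1 gives 20 non-critically ill and 20 critically ill patients: 20 + 20 = 40, which agrees with section 4.1. It also states "Assuming a case fatality rate of 50% in the critically ill group, we anticipate to include 10 patients" for post mortem analysis: 20 × 0.50 = 10. Both figures reproduce, and the point changes neither. The study is declared exploratory and the protocol gives no power calculation to check.

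**The two definitions side by side.**

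| Patient with a positive test, adult, not pregnant | Section 2.3 | Section 3.1 |
|---|---|---|
| Ward patient admitted for COVID-19 | eligible | eligible |
| Ward patient admitted for another brain disease | not eligible | eligible |
| Ventilated ICU patient admitted for COVID-19 | eligible | eligible |
| Ventilated ICU patient admitted for another brain disease | not eligible | eligible |
| Out-patient who can travel without public transport | eligible | eligible |

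The sections differ in rows two and four only, so the contradiction is confined to inpatients. Pre-existing CNS disease is a separate matter. A patient with an old stroke or dementia who is admitted for COVID-19, or who comes as an out-patient, is eligible under both sections. Aligning 3.1 with 2.3 would not touch those patients.

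**Weight of one patient.**
- One cohort: 1/20 = 5 percentage points.
- Whole study: 1/40 = 2.5 percentage points.
- Expected autopsy set: 1/10 = 10 percentage points.

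**How likely at least one such patient is.** The documents give no share q of participants with a positive test and another brain disease. The values below are assumptions, chosen to show a range. The expected number is 40 × q. The chance of at least one among n patients is 1 − (1 − q)^n.

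| Assumed q | Expected among 40 | At least one among 40 | At least one among 20 ICU patients | At least one among 10 autopsies |
|---|---|---|---|---|
| 2% | 0.8 | 55% | 33% | 18% |
| 5% | 2 | 87% | 64% | 40% |
| 10% | 4 | 98% | 88% | 65% |
| 20% | 8 | about 100% | 99% | 89% |

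For example, at q = 5% and n = 40: 1 − 0.95^40 = 0.871. The autopsy column assumes the same share among those who die. It also ignores the wording in section 2.3 that ties autopsy to disease-related death, so it is an upper illustration.

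**The case against.** The best reply is that 2.3 and 3.1 can be read together: the reason-for-admission condition is already in the protocol, and 3.1 speaks of COVID-19 patients. Several safeguards also bear on attribution. Neuroradiologists read for encephalitic changes, and an old infarct or a contusion is not one. A board-certified neurologist examines the patients and symptoms are documented. Viral RNA is tested in CSF and plasma. Ward recruitment runs through Internal Medicine, which makes a stroke or trauma admission less likely there. Detailed definitions of the affected group may sit in a statistical analysis plan that is not at hand.

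Much of this stands, and it limits the size of the point. It does not remove it. Eligibility belongs in the protocol, and the list that screens patients omits the condition. The ICU route stays open. The radiological reading filters MRI findings, but it does not filter neurological scores, CSF markers or the affected/unaffected grouping.

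A reader might infer more than the documents support:
- **That 3.1 admits any adult with a positive test.** It also excludes pregnant women and out-patients who depend on public transport, and the critically ill cohort must need ventilation.
- **That every endpoint is distorted.** The argument reaches the affected/unaffected comparison. It does not show distortion of, for instance, peripheral blood mass cytometry as such.
- **That 3.1 conflicts with the risk section because it does not exclude people unsuited to lumbar puncture, MRI or contrast.** Naming contrast allergy as a risk in 6.2 contradicts nothing. Section 2.3 promises MRI safety precautions and lists gadolinium as optional, and 4.2 says incomplete data will be reported.
- **That everyone with prior CNS disease should be excluded.** That trades recruitment and representativeness for purity, and nothing in the documents settles the trade.

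**Conclusion.** The point holds as an inconsistency between sections 2.3 and 3.1 for inpatients, with a consequence for the main comparison in 4.1. As written, 3.1 can place patients with another brain disease in the affected group, and nothing in 4.1 sets them apart. Textually this is certain.

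The size is not known. Each such patient carries 5 percentage points of a cohort of 20, but how many there would be depends on a share the documents do not give. The direction for the proportion affected is upward; for individual markers it could go either way. These directions assume that another brain disease usually produces a deficit visible on examination, and that no unseen definition already removes such patients. The correction is worth making because it is cheap before recruitment and hard to make afterwards if the history was not recorded.

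**What to change.** 1. In section 3.1, add for inpatients the condition already in 2.3, that COVID-19 is the reason for admission. Leave the out-patient criteria as they are.
2. Record pre-existing and concurrent CNS disease at enrolment for all participants, out-patients included.
3. In section 4.1, state that pre-existing deficits and lesions do not count as COVID-related when patients are grouped as affected or unaffected.
4. Show the key comparisons with and without patients who have pre-existing or concurrent CNS disease.

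Steps 2 to 4 are needed because step 1 alone leaves in patients with earlier CNS disease who are admitted for COVID-19 or come as out-patients. The cost is a short amendment, one history field and one sensitivity analysis. Inpatients with incidental positive tests are lost; they are probably few, but the documents give no figure. With at most 20 per cohort, the analysis without these patients will be imprecise and should be read as a check on robustness.

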### **3.2 Recruitment, screening and informed consent procedure**

Recruitment takes places at University Hospital of Basel. Critically ill patients are going to be recruited at the Intensive Care Unit (ICU), modestly ill patients are going to be recruited from "normal" hospital ward through the project leader.

In case of hospitalized patients that can not be informed, we are going to inform their relatives about the study procedures.

Recruitment procedure is supported from clinical departments of the ICU (Prof. [name]) (critically ill patients) and Internal Medicine (Prof. [name]) (modestly ill patients).

Patients who got tested COVID-19 positive in the ambulatory test centre of the University Hospital of Basel will be handed an information sheet about this project including our contact information. Should they be interested in participating, they can send an email including their name, surname, phone number and date of birth to an email account specifically created for this project ([contact]). Afterwards they will get a phone call, where they will be informed in detail about the procedures that take place and their risks and benefits. If desired we are also able to organize a skype or zoom call.

If they agree, they will receive the patient information and agreement via email or by post and an appointment date will be set for the study procedures. The study agreement has to be printed and signed. The out-patients will have to bring it along to the appointment date for the study procedures. In case they are not in charge of a printer or they forget to bring the signed agreement along, we prepare printed versions of the information and agreement sheet. Then it can be read and signed directly at the University Hospital of Basel during the appointment. For this case we include an extra hour before study procedures start. During this time the out-patients can go through the information again and ask further questions.

Because the out-patients incur a hospital stay only for their participation in this project they will get paid with an amount of 200 CHF.

Concerning the commute to the hospital, we will give precise advice as to how to reach the hospital. We will suggest to take the car, walk or take the bike. Also they will be informed to wear a mask at all times as soon as they leave the house. Should public transport be their only option, they will be excluded from the study. These advices apply for the way home as well.

For informed consent process, the study is going to be explained to the potential participant verbally, providing all pertinent information (purpose, procedures, risks, benefits etc.) with ample opportunity to ask questions.

Following the verbal explanation, the potential participant is going to be provided with a study information sheet. To consider whether or not to participate in this research sufficient time is going to be afforded (adapted on how long it reasonably takes to evaluate the procedures, risks, benefits etc.).

After the potential participant had time to read the study information sheet, the Investigator is going to answer any additional questions. For participation in the research the participant's agreement is going to be recorded on the study information sheet. The potential participants will have 24h time to decide their participation.

In case of potential participants who are unable to listen, read and write, the study is going to be explained to their relatives. We will inform the relatives by telephone about this project and make an appointment (at University Hospital of Basel) for informed consent process.

In case of death, the relatives of the participant are going to be asked for consent to perform autopsy at the institute of pathology, University Hospital of Basel. The relatives are going to be contacted by telephone to make an appointment (at University Hospital of Basel) for informed consent process regarding the autopsy regulations at the institute of pathology. Informed consent process for autopsy takes place in accordance with the standard procedure of the University Hospital of Basel.

